**Figure 3. F3:**
[figure not shown]
Example of the INTeRAcT program for one week: the therapy program is structured in daily six-hour sessions, comprising the following seven components: (1) UL, (2) LL, (3 and 4) UL/LL + TECH, (5) cardio, (6) goal-oriented therapy, and (7) self-management education. Cardio: cardiovascular fitness training; LL: lower limb therapy; TECH: therapy with technological devices for the upper or lower limb; UL: upper limb therapy.

Upper and lower limb therapy sessions without technology (components 1 and 2) follow a conventional therapy approach and include a range of techniques such as mobilization and stretching of the affected limb, analytical and coordination exercises, strength training, task-specific training with repetitions, fall prevention, balance training, and functional exercises. These sessions incorporate both proximal and distal components, emphasizing fine manipulation, sensorimotor training, foot placement, analytical movements, gait adaptability, and complex ADLs. Both upper and lower limb therapy components are provided daily, 1 hour each, for a total of 5 hours per week per component.

In addition to conventional upper and lower limb therapy, participants participate in technology-assisted upper and lower limb therapy (components 3 and 4), with 1 hour per day dedicated to each component. For upper limb rehabilitation, the Gloreha (BTL Robotics) focuses on improving distal hand function through passive or active-assisted mobilization of the fingers. Action observation and interactive games are integrated to stimulate arm and hand use while providing arm support. The OmniHi5 (ACP) uses electrical stimulation to facilitate upper limb movement. The HUR fitness equipment is adapted for individuals in wheelchairs for strength training, but can also be used by ambulatory individuals with a standard chair. For lower limb rehabilitation, an exoskeleton gait robot (Ekso Bionics) assists individuals with limited or no walking ability, whereas the ZeroG Gait & Balance System (Aretech) provides dynamic body weight support in a fall-safe environment to facilitate gait training. The RehaMove (Hasomed), a functional electrical stimulation bike, is used to activate muscles and promote movement. Additionally, the DIERS 4Dmotion Lab integrates a treadmill with a feedback system to improve weight shifting and promote a more normal gait pattern. To complement these technologies, the D-WALL Elite (TecnoBody) offers a versatile platform for designing personalized exercises and managing a broad range of programs focused on posture, functional training, balance, and strength. These advanced technologies are integrated into therapy to align with the participant’s individual rehabilitation goals.

The cardiovascular fitness training [99-101] (component 5) focuses on interval training, using a variety of methods such as a bicycle or arm ergometer, stepping, and Tabata (eg, boxing, circuit training, and ropes). The training intensity is primarily monitored using heart rate. In individuals with complete or incomplete SCI, where muscle mass is limited, the intensity is guided by the Borg Rating of Perceived Exertion Scale [102], aiming to achieve a score of at least 12 of 20. This training is delivered in a group setting for a total of 2.5 hours per week, consisting of one 1-hour session and three 0.5-hour sessions.

During the goal-oriented training session [103] (component 6), the therapist and participant collaboratively design and execute an individualized therapy plan based on the three specific goals previously established. These goals follow the SMART (Specific, Measurable, Achievable, Relevant, and Time-Bound) principles. For example, a goal might be: “After three weeks of training, I want to be able to walk 2 km with my dog.” This approach ensures that therapy is tailored to the participant’s needs and integrated into a highly functional, real-life context. The goal-oriented training is conducted daily, with 1 hour of individual sessions each day, amounting to a total of 5 hours per week.

The self-management sessions (component 7) are based on key principles that emphasize a personalized and flexible approach. It tailors support to individual needs and circumstances, allowing for initiation at any stage. The approach prioritizes the person’s story and promotes supportive relationships while encouraging autonomy. Emphasis is placed on small, meaningful actions in daily life, reinforcing autonomy and motivation. It builds on individuals’ existing self-management strategies and social support systems to enhance long-term engagement and adaptability [104]. Self-management sessions comprise a total of 2.5 hours per week, including 1 hour of group session and 3 individual sessions of 0.5 hours each. Group therapy allows participants to learn from each other and exchange experiences and strategies, while individual sessions provide personalized counseling tailored to each participant’s needs and goals.

During the 3-week intervention period, the intensive therapy is documented daily in diaries by the physiotherapists, including the total number of minutes of therapy, the division between active therapy time (eg, performing active repetitive movements) and other therapy time (eg, explanation, resting periods, and ADL tasks), and the content of each of the 7 therapy blocks. Additionally, at the end of each therapy block, the Borg Rating of Perceived Exertion Scale [105] is completed to assess participants’ subjective experiences of physical exertion. This scale ranges from 6 (“no exertion at all”) to 20 (“maximal exertion”) and allows for individualized adjustments to training intensity. Outside the 6-hour daily intervention sessions, participants were permitted to continue their usual care, which was recorded in diaries. The intervention was described according to the TIDieR (Template for Intervention Description and Replication) checklist, provided in Checklist 1.

#### Control Intervention: Usual Care

To allow a pragmatic comparison with current clinical practice, the control group will continue their usual care at home or in an outpatient rehabilitation center or hospital for the entire 9-month study period, without receiving any alternative interventions. After completing this study, participants in the control group will be given the opportunity to receive the identical 3-week program following the final follow-up measurement at 9 months. This waitlist-control design will help maintain participants’ motivation to adhere to this study during the 9-month follow-up period.

Participants will document their usual care in therapy diaries (Figure 1), with assistance from their therapist if needed. These diaries will capture the frequency (number of sessions), intensity, and time (duration), and type (therapy content) of physiotherapy, occupational therapy, and psychological sessions, in line with the FITT (Frequency, Intensity, Time, and Type) principles [101]. The diaries were developed by the research team based on expert input, and their content was reviewed and approved by clinicians. Participants in the intervention group will complete the same diaries during the follow-up period, after the 3-week intervention. The diaries will be collected and reviewed monthly, and any missing data will be requested from participants.

### Adverse Events

The risk of adverse events (AEs) occurring during this study is considered low; therefore, safety reporting will be limited to the safety reporting that is necessary in routine care. Participants will be asked to report any AE related to this study-specific intervention to this study’s team. This study’s team will keep detailed records of all reported AEs, which will be assessed by the investigator at the rehabilitation site, an MD, regarding their seriousness, causality, and expectedness. A structured procedure has been established to ensure proper reporting of AEs to the relevant regulatory committees. If an AE directly or indirectly related to study participation requires additional medical care, the associated costs will be covered by this study’s insurance.

The following events are commonly observed and are therefore not considered as AEs for this study: (1) during or after the treatment, the participant may feel the following symptoms or events: fatigue, muscle spasm or increase in muscle tone and soreness, as with any movement exercise with a device that activates the body and muscles. These types of symptoms are anticipated and should fade out; (2) redness of the skin, light bruising, or small superficial pressure injuries where the equipment has exerted pressure on the skin, from harnesses or use of the revalidation robots. These injuries will be subject to follow-up as they are in usual care: close monitoring by the therapist and use of pressure bandages to prevent them; (3) orthostatic hypotension: blood pressure drop due to position change (usually due to verticalizing: sitting or lying to standing); and (4) changes in bladder and bowel control after activation of the participant.

Premature discontinuation or interruption of the intervention may occur due to AEs, protocol violations, pregnancy, or illness. In such cases, clinical follow-up will be ensured, and if illness interferes with therapy, continuation or restarting the intervention will be considered where feasible.

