#### Data: Costs and Utilities

This evaluation will incorporate costs and effects during this trial and follow-up period, adopting both health care and societal perspectives. Both perspectives will include costs covering expenses borne by health insurance as well as patient copayments. The health care perspective will include all direct costs, both medical and nonmedical, while the societal perspective will encompass all costs, including direct medical and nonmedical costs as well as indirect costs.

The direct medical costs include all costs for treatment and follow-up from the health care perspective, and all out-of-pocket contributions by the participant. The following types of resource use will be collected: primary care visits, emergency visits, inpatient stays, outpatient services, medication, diagnostic tests, and medical or ADL aids.

Direct nonmedical costs include transportation and accommodation expenses, as well as home care assistance.

Indirect costs comprise productivity loss (eg, number of days away from work) and productivity losses due to informal caregiving. The productivity losses of the participants and informal caregivers will be valued using the human capital approach [134]

The effects will be expressed in Quality-Adjusted Life Years (QALYs). To calculate QALYs, health-related quality of life (QoL) scores are multiplied by the length of time spent in a particular health state. For example, 1 QALY represents 1 year of life in perfect health. Health-related QoL will be collected through the EQ-5D-5L questionnaire [113] and quantified in utilities derived from the national values of the EQ-5D-5L [135]. QALYs will be calculated using the area under the curve method.

To estimate the costs corresponding to the participants’ resource use, participants will be asked to provide invoices related to these expenses to ensure accurate cost reporting. Additionally, national tariffs will be used for valuation (NHIDI, BCFI, National feedback reports on hospitalizations, national cost per working hour, national cost for transportation, etc).

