### Ethical Considerations

#### Ethical Approval

This study obtained ethical approval from the Ethics Committee Research of KU/University Hospitals Leuven, Belgium (registration number: B3222021000614, internal reference: S67164), as well as from the local ethics committee of the site, AZ Herentals, on June 13, 2023. This study will be conducted in accordance with the Declaration of Helsinki. The currently approved protocol is version 5, dated March 15, 2024. All participants provide written informed consent before enrollment (Multimedia Appendix 1). No financial compensation was provided aside from 3 weeks of free high-dose therapy and reimbursement of expenses (eg, transport costs).

Throughout the clinical trial, an annual progress report (or additional reports upon request) will be submitted to the ethics committee, providing an overview of all (serious) AEs that occurred during the reporting period, along with newly available safety information. This study will adhere to the approved protocol, current International Council for Harmonisation and International Council for Harmonisation–Good Clinical Practice guidelines, applicable regulatory requirements, the European General Data Protection Regulation 2016/679, and relevant Belgian laws implementing the General Data Protection Regulation. The currently approved protocol is version 5, dated March 15, 2024. Protocol amendments will be submitted to all involved ethical committees. This protocol was developed following the SPIRIT (Standard Protocol Items: Recommendations for Interventional Trials) 2013 checklist (Checklist 2).

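### Adverse events are solicited by their relatedness to the study intervention, which controls do not receive, so reported AE counts are not comparable between arms and do not supply the full overview promised to the ethics committee

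*Protocol article*

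**What the plan says.** The Adverse Events section of the protocol article considers the risk low and concludes that "safety reporting will be limited to the safety reporting that is necessary in routine care". The solicitation rule follows: "Participants will be asked to report any AE related to this study-specific intervention". Events that are reported are recorded and then "assessed by the investigator at the rehabilitation site, an MD, regarding their seriousness, causality, and expectedness". The same section lists symptoms, skin injuries, blood-pressure drops and bladder or bowel changes under this rule: "The following events are commonly observed and are therefore not considered as AEs for this study".

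Under Control Intervention: Usual Care, controls continue usual care "for the entire 9-month study period, without receiving any alternative interventions". They may "receive the identical 3-week program following the final follow-up measurement at 9 months".

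Under Ethical Approval, the annual report to the ethics committee is described as "providing an overview of all (serious) AEs that occurred during the reporting period".

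Under Data: Costs and Utilities, the resource use collected for the economic evaluation includes "primary care visits, emergency visits, inpatient stays, outpatient services, medication, diagnostic tests". The Health Economic Evaluation section says that costs are gathered over the 9 months by diaries in the first and ninth periods and by monthly questionnaires between them. These are reviewed monthly, and participants are contacted about gaps. The trial-based analysis uses individual data from both arms.

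**The concern.** The participant is asked about events that are already linked to the intervention. The physician's causality assessment comes after that filter and applies only to what was reported, so it cannot recover an event that nobody linked to the program. Participants know their allocation after T0 (Randomization and Blinding), and controls have no study program to link an event to.

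The trial is described as phase III and aims to support reimbursement and wider implementation of 30 hours of training per week. Readers of the results will look for a statement on safety. A short AE list could reflect the collection rule, and a longer list in the intervention arm could not be set against a background rate in controls. Either could be misread unless the report says how the counts arose.

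**Working it through.** The documents give no AE rate or AE sample size, so there is no figure of the plan's own to reproduce. The check compares sections and then adds an illustration.

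**Sections side by side**

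1. Adverse Events: participants are asked for events related to the study intervention.
2. Control Intervention: Usual Care: controls receive no study intervention until after the 9-month measurement. Under item 1, the expected number of control AEs during the comparison is close to zero whatever their true event rate.
3. Adverse Events: seriousness, causality and expectedness are judged on reported AEs. This step cannot add events that item 1 did not elicit.
4. Ethical Approval: the annual report covers all (serious) AEs that occurred. The article describes no route by which unrelated or control-arm events would enter that report, so items 1 and 4 do not fit together as written.
5. Adverse Events: several common consequences of training are defined as not being AEs. This removes events mainly from the intervention arm, which works in the opposite direction to item 2.
6. Data: Costs and Utilities and Health Economic Evaluation: emergency visits and inpatient stays are recorded in both arms, whatever their cause.

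**Illustration of items 1 and 2**

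Inputs: 50 participants per arm (Randomization and Blinding). The true risk p and the captured fractions c are assumptions: p from 10% to 40%, equal in both arms; c from 50% to 100% in the intervention arm and from 0% to 10% in controls.

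Expected participants with a recorded AE = 50 × p × c. Apparent risk difference = p × (c_int − c_ctrl). The true difference is zero.

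| p | c_int | c_ctrl | Intervention | Control | Apparent difference |
|---|---|---|---|---|---|
| 10% | 50% | 10% | 50 × 0.10 × 0.50 = 2.5 | 50 × 0.10 × 0.10 = 0.5 | 4 points |
| 20% | 80% | 5% | 50 × 0.20 × 0.80 = 8.0 | 50 × 0.20 × 0.05 = 0.5 | 15 points |
| 40% | 100% | 0% | 50 × 0.40 × 1.00 = 20 | 0 | 40 points |

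In the middle row the chance that the control arm records no AE at all is (1 − 0.20 × 0.05)^50 = 0.99^50 = 61%.

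**The error can also run the other way**

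Suppose the true risks were 40% and 10%, a difference of 30 points, and capture were 50% and 5%. Recorded risks would be 0.40 × 0.50 = 20% and 0.10 × 0.05 = 0.5%, an apparent difference of 19.5 points. The rule would then understate a real excess. The list of events not counted as AEs adds to this possibility.

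**The case against.** The strongest reply has four parts.

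**Other sources may exist.** The section does not say that participants are the only source or that other events are refused. Intervention participants spend six hours each weekday with physiotherapists who keep daily diaries. Insurance cover extends to events indirectly related to participation. A structured reporting procedure is mentioned, and approved protocol version 5 is not shown. The promise under Ethical Approval could itself mean that the full protocol collects more. This stands as far as it goes: a reader might infer that only participant-attributed events are ever recorded, and the article does not establish that. It does state the solicitation rule affirmatively, however, and describes no route for control-arm events.

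**No safety comparison is promised.** The aims, hypotheses and clinical analysis contain none. This also stands. The point is a weakness of design and reporting and does not contradict a stated analysis.

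**Safety can be compared to some extent.** A reader might infer that the trial cannot compare safety between arms at all. That goes too far, because emergency visits and inpatient stays are collected in both arms, and fatigue severity is a secondary outcome in both. What cannot be compared is reported AEs.

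**The size is not measurable from the documents.** The illustration rests on assumed risks and capture fractions. A reader might instead use the bound for zero events in 50 participants, 1 − 0.05^(1/50) = 5.8%, as a measure of the defect. It is not one: it reflects the sample size and would be the same with perfect collection. Nor do the documents show that the bias favours one arm, because the list of events not counted as AEs offsets the missing control events.

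**Conclusion.** The point holds for reported AEs. Solicitation by relatedness, combined with a control arm that has no study intervention for 9 months, makes AE counts non-comparable between arms. The rule as written does not deliver the overview described under Ethical Approval, and the two sections must be reconciled.

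The asymmetry follows from the text alone; its size does not. At equal true risk, the assumed ranges give 2.5 to 20 of 50 intervention participants and 0 to 2 of 50 controls with a recorded AE, an apparent difference of about 4 to 40 percentage points. The net direction of the error is uncertain in practice. The conclusion assumes that the full protocol has no collection route that treats both arms alike; if it has one, the article should say so. The matter deserves correction because analysis is still ongoing and usable data from both arms exist.

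**What to change.** Data collection ended in July 2025, so AE elicitation cannot be changed. The changes belong in analysis and reporting.

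1. **Reconcile the two sections.** State by what route, if any, unrelated and control-arm (serious) AEs reached the annual ethics report. If there was none, describe the overview as limited to the events that were solicited.
2. **Add one descriptive table by arm**, irrespective of relatedness: emergency visits and inpatient stays over the 9 months from the resource-use data, with rate differences and 95% CIs. Split it at T1 only if entries are dated. Take deaths from trial and dropout records, since the listed cost items do not include them. Show the completeness of the data by arm.
3. **Report intervention-related AEs separately** for the intervention arm, and list the event types that were not counted as AEs.
4. **State the limitation plainly**: reported AE counts must not be compared between arms or read as evidence of safety.

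The cost is some coding work and one table, with no new data collection from participants. The resource-use events are unadjudicated and may be incomplete for dropouts. The article does not show that reasons for visits were recorded, so the table is a crude proxy and should be labelled as such.

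### Common events are removed from the AE definition before seriousness is judged, and orthostatic hypotension and bladder or bowel changes carry no severity limit

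*Protocol article*

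**What the plan says.** The Adverse Events section considers the AE risk low and keeps safety reporting to what routine care requires. Participants are asked to report AEs related to the study intervention. The team records what is reported, and a physician at the rehabilitation site judges seriousness, causality and expectedness.

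The section then sets an exemption: "The following events are commonly observed and are therefore not considered as AEs for this study". Four groups follow:

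1. "fatigue, muscle spasm or increase in muscle tone and soreness", with the comment "These types of symptoms are anticipated and should fade out".
2. "redness of the skin, light bruising, or small superficial pressure injuries" at sites of equipment pressure, to be followed up as in usual care.
3. "orthostatic hypotension: blood pressure drop due to position change", usually on being brought upright.
4. "changes in bladder and bowel control after activation of the participant".

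The section adds: "Premature discontinuation or interruption of the intervention may occur due to AEs", along with other reasons such as illness. Under Ethical Approval, the annual progress report is described as "providing an overview of all (serious) AEs that occurred during the reporting period".

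**The concern.** Whether an event is expected and whether it is serious are separate questions, and the section itself lists them as separate judgements for the physician. The exemption lets the first question settle the second: an event of a common type leaves the AE definition before anyone asks how bad it was.

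For minor, passing reactions to exercise this is a sensible way to keep the AE log usable. It becomes a problem where the exempted category has no upper limit. The intervention is six hours of training each weekday, includes exoskeleton gait training for people with little or no walking ability, and is open to people with SCI of grades A to D. The exempted events are those the article itself calls common with this treatment. The trial is meant to inform reimbursement, so its harms record should be able to show a severe or lasting form of such an event if one occurred.

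**Working it through.** No arithmetic applies: the article gives no AE rate, and the point turns on a definition. The check is whether a serious form of each listed event can reach medical review under the text as written.

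**Step 1. Ground for the exemption.** It is frequency alone ("The following events are commonly observed and are therefore not considered as AEs for this study"). The sentence does not mention severity, seriousness or duration.

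**Step 2. Limit within each group.**

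| Group | Wording that limits it | Is a serious form exempt as written? |
|---|---|---|
| Fatigue, spasm, tone, soreness | "These types of symptoms are anticipated and should fade out": an expectation, not worded as a condition | Unclear; can be read as transient symptoms only |
| Skin events | Light bruising; small and superficial pressure injuries | No: bruising and pressure injuries beyond those limits are not in the list |
| Orthostatic hypotension | None | Yes |
| Bladder and bowel changes | None | Yes |

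The skin item shows that a limit could be written into the list. The last two items have none.

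**Step 3. Who gets assessed.** The physician's assessment of seriousness, causality and expectedness applies to reported AEs. An event that is not an AE has no stated route into it.

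**Step 4. Any route back.** Nothing in the article returns a listed event to AE status because it was serious, persisted, needed medical care or stopped therapy.

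**Step 5. Consequence.** From steps 1 to 4, a severe orthostatic episode or a lasting change in bladder control is not an AE under the rule. It is not assessed, and it is absent from the yearly overview because that overview covers (serious) AEs. The AE count omits it by construction.

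**The case against.** The strongest reply is that the list plainly describes ordinary reactions to exercise and that nobody would apply it to a serious event. The article condenses a longer approved protocol (version 5), refers to a structured procedure for AE reporting and commits the trial to Good Clinical Practice. An override for serious expected events may sit in those documents. This is a fair limit on the finding, but the article states the exemption as a rule and does not merely omit detail. If an override exists, one sentence citing it resolves the point.

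Second, a fall or injury following a pressure drop is a different event and could be reported as its own AE. That is possible, though the text does not say so, and a lasting continence change need not produce any separate injury.

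Third, some of these effects are seen elsewhere. The FIM-motor and SCIM score bladder, bowel or sphincter management at T0, T1 and T2 in both arms. The Fatigue Severity Scale covers fatigue, and emergency visits and inpatient stays enter the cost data whatever they are called. This stands as partial capture, but none of it is a judgement of seriousness or causality for an individual event.

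A reader might also infer that the exemption contradicts the promised (serious) AE overview and the sentence naming AEs as a reason for discontinuation. It does not: both statements are consistent with a narrow AE definition and simply inherit it. Nor does the article support saying that the understatement falls only on the intervention arm. Participants are asked only for AEs related to the study intervention, and no between-arm AE comparison is described.

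**Conclusion.** The point holds as a flaw in a stated reporting definition. It is firmest for orthostatic hypotension and for bladder and bowel changes, which have no limit at all. It is weaker for fatigue, spasm and tone, where the remark about fading can be read as confining the exemption to transient symptoms. It does not apply to the skin items' minor-injury wording.

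The direction is clear: AE counts may be too low. The size is unknown. A reader might be tempted to multiply an assumed event rate by the 50 planned intervention participants, but nothing in the article supports any particular rate, so no number of missed events should be quoted.

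The conclusion assumes that the rule was followed as written and that the full protocol holds no exception for serious listed events.

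**What to change.** Restrict the reporting exemption to mild, transient forms of the listed events. Add that any listed event that was serious, required additional medical care, or interrupted or ended the intervention is counted as an AE and receives the planned assessment of seriousness, causality and expectedness. If the full protocol already says this, cite it in the report. This changes only what is counted and assessed, not how participants are managed.

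The last clinical visit was in July 2025 and analysis is ongoing, so the definition must be applied to what is already held: reported events, any recorded reasons for discontinuation or interruption, and the emergency and inpatient resource-use data. Therapist diaries should not be relied on for this. They are described as recording minutes, therapy content and perceived exertion, not symptoms.

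The results paper should state that the exemption was in force during data collection and that milder listed events were not systematically captured.

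The cost is one or two sentences, some record review and a slightly higher AE count. Retrospective capture will be incomplete: resource-use data can flag candidate events but cannot establish cause, and events never recorded may not be recoverable.
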